**Fig. 1 Fig1:**
[figure not shown]
Study design to evaluate the effect of a new EBF counselling intervention in overweight women. Abbreviations: Infant Feeding Intention Scale (IFIS), Middle Upper Arm Circumference (MUAC), Food Frequency Questionnaire (FFQ), International Physical Activity Questionnaire Short Version (IPAQ SV), Edinburgh Postnatal Depression Scale (EPDS)

**Fig. 2 Fig2:**
[figure not shown]
Timeline measurements and breastfeeding support for intervention and control groups. Secondary outcomes include breast milk sample and maternal serum sample. Other variables include maternal physical activity (IPAQ SV) and maternal food intake

### Study population

Pregnant women in the last trimester of gestation who meet the inclusion criteria and provide written informed consent (for vulnerable populations) will be recruited from the pregnant care program (CAPS) in a Baby Friendly Hospital in Bogotá, Colombia; the hospital is a referral institution for maternal and child care, where the prevalence of overweight pregnant women is 34.6%. The prevalence of obesity in children under 5 years in 2010 using BMI/age was 5.2% in Colombia and 6.4% in Bogotá. The hospital reported a population coverage of 1,620,000 for December 2016, and a total of 591 pregnant women in the program of Friendly Services in Sexual and Reproductive Health with a high proportion in the lowest socioeconomic groups.

The inclusion criteria will be:

*Women:* singleton pregnancy, overweight for gestational age (defined as BMI/GE ≥ 28.1 kg/m^2^ using Atalah’s criteria) measured at the 32nd week of gestation, older than 18 years, no pre-eclampsia or diabetes, permanent residence in Bogotá and intention to breastfeed. Women with hypertension during labour who do not require admission to the intensive care unit will be included in the study. Women with a history of breast surgery, maternal intensive care stay, postpartum depression risk at baseline (late pregnancy) based on the Edinburgh Postnatal Depression Scale (EPDS) [54], infection with human immunodeficiency virus (HIV) or treatment with cytotoxic drugs, cardiovascular medications, anticoagulants or psychopharmaceuticals will be excluded.

*Infant*: healthy term newborns (≥ 37 weeks), birth weight ≥ 2500–4000 g without any condition that interferes with breastfeeding practice such as galactosemia, cleft lip and/or cleft palate and congenital heart defect or disease.

### Sample size

The sample size was calculated to detect a difference in the prevalence of EBF between the intervention and control group of 23%, based on literature [43] reporting a baseline EBF of 22.8% in the control group (the prevalence of EBF for the Colombian population at 4 months in urban areas in 2010 [55]; there is a lack of data on EBF prevalence in overweight women in Colombia), with a power of 95%, an alpha error of 5% and a two-tailed calculation determined using the EpiInfo StatCalc program [56]. Assuming follow-up losses of 20%, 290 woman-child dyads are required, 145 in each group.

A convenience subsample of 60 women will be recruited, 30 from each group (20% of overall sample) for analysis of serum and milk prolactin concentration and macronutrient content.

### Recruitment

Overweight pregnant women (using Atalah’s criteria: BMI/GE ≥ 28.1 kg/m^2^) [57] will be contacted at 32 weeks of gestation at their hospital antenatal check-up. They will receive information about the study; those who agree to participate will be asked to provide written informed consent. To protect the identity of the women, they will be assigned an identification or ID number. Assistance with travel expenses for each visit to the clinic will be provided, and at the end of the study they will receive a gift to thank them for their participation in the study.

#### Randomization and masking

Each overweight woman will be assigned randomly to one group, intervention (breastfeeding counselling intervention) or control (standard counselling). Randomization assignments will be prepared by a member of the team who has no contact with the study subjects, using randomized blocks. Assignments will be stored in sealed opaque envelopes. It will not be possible to blind the researcher performing the intervention and collecting data, although laboratory measurements will be blinded. Mothers will be aware that the study involves assignment to one of two types of breastfeeding support but they will not know the details of this support. They will have the possibility to withdraw from the study at any time. To avoid contamination between groups, appointments will be scheduled individually by telephone contact.

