#### Primary outcomes and variables

Outcomes will be measured at birth (baseline) and 1, 3 and 4 months postpartum in the intervention and control groups. The primary outcomes are:
i)Prevalence of breastfeeding and EBF, ascertained by asking the mother about infant feeding practices during the last 24 h;ii)Growth velocity from birth, defined as change in weight for length in g/cm and length for age in cm/days;iii)Maternal weight loss after delivery in kg, using maternal weight at 24 h as baseline.

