#### Measures

Questionnaires and assessments will be used to collect information among intervention and control groups at specific time-points, as shown in Table 1.
Maternal socioeconomic and demographic information, pregnancy information and paternal information: Information about residency, age, marital status, occupation, socioeconomic level, family size, family income, educational level, maternity leave, access to public services, social security, health benefits, smoking, alcohol consumption, family and medical history will be recorded. Gestational age will be determined by the date of the last menstruation, corroborated by sonographic studies available in the clinical notes. Paternal information will be reported by the woman and will include health status and monthly income.Intention to breastfeed: The scale uses five simple questions to determine the method of feeding that the woman plans for the baby. The scale has been validated and translated in previous studies [60].Maternal anthropometry: Anthropometric data - weight, height and mid upper arm circumference (MUAC) - will be collected in the last month of pregnancy, 24 h postpartum, and 1, 3 and 4 h months postpartum in minimal clothes. Weight will be measured in duplicate using an electronic scale (SECA 813, capacity 200 kg, precision 100 g), height measured in triplicate using a portable stadiometer (SECA 213, up to 205 cm) and MUAC measured in triplicate to the nearest cm (SECA 203 measuring tape, range 0 to 205 cm, graduation 1 mm). Weight gain during gestation (self-reported weight at the end of gestation minus pre-gestational weight) will be used as a baseline characteristic and as a covariate to predict the main outcomes.Breast examination: Participants will complete a questionnaire using illustrations of breasts to identify possible anatomical aspects that could make breastfeeding difficult (e.g. large breasts, flat nipples). This information will be used to focus the intervention for individual mothers.Edinburgh Postnatal Depression Scale (EPDS): This consists of 10 questions about feelings during the last week. It will be administered during the last month of gestation and 1 month postpartum as a tool to determine the risk of postpartum depression [54].Counselling register and evaluation: To assess the content of and adherence to the new EBF counselling intervention, a record of the problems identified will be kept during each visit. A questionnaire will also be administered by an independent investigator blinded to group allocation at the end of the study period (four months postpartum) which will include information on the problems identified, solutions and success, measured as: not successful (no problem resolution); limited success (partial resolution of the problem), or successful (problem solved).IPAQ short version: Physical activity questionnaire which considers types of physical activity, time (minutes per day) and number of days per week, and number of hours per day that the woman remains seated [61].Maternal food consumption: Determined using a standard food frequency questionnaire used and adapted in Colombian populations in other studies, and two multiple steps 24-h recall questionnaires to determine food consumption and nutrient intake including supplements, vitamins, minerals and maternal feeding problems; to be used as a baseline descriptive characteristic and as a potential confounder. This methodology is based on that described by the United States Department of Agriculture [58, 59]. To improve the quality of the data, photographs will be used to determine portion size [70]. Data analysis will be conducted using Colombian food composition tables [71], USDA standard nutrient reference database and food labels.Delivery information: Data about the type of delivery, newborn APGAR score, time of breastfeedng initiation, maternal-infant complications including those which delay the initiation of breastfeeding, and drugs administered during labour and the first 4 months after delivery.Newborn and infant anthropometry: Anthropometric variables - weight, length, MUAC and head circumference - will be measured by a trained nutritionist and dietitian following WHO protocol [72] at birth and 1, 3 and 4 months postpartum. Infant weight will be measured in duplicate using an electronic baby scale (TANITA 1583 with precision of 10 g, capacity 200 kg), length measured in triplicate using an infantometer (SECA 417, folding mechanism and foot stop, measuring range up to 100 cm), and head circumference and MUAC measured using a pediatric tape measure (SECA 201, range 0 to 205 cm, graduation 1 mm). Infant growth velocity will be defined as the change in the Z-score of weight for length, length for age, head circumference for age and mid upper arm circumference for age from birth to four months according to WHO growth standards [73]. Data collection will be performed by the same researcher in both groups to control information bias among observers.Breastfeeding information: This questionnaire collects information about initiation of breastfeeding at the hospital.Infant 24-h dietary recall: To determine the EBF prevalence, an infant 24-h recall will be used asking mothers about the foods consumed by the child during the previous day and infant feeding practices at 1, 3 and 4 months. = The counsellor will ask about the initiation, frequency and mode of preparation of specific beverages and semisolid foods or supplements since the last visit. This methodology will allow breastfeeding to be classified as exclusive or predominant according to WHO definitions [12].Breast-latching observation: Considers information about position of breastfeeding and maternal-infant perception of comfort during breastfeeding. This is a check-list that the investigator completes after watching a breastfeed [74].Breast milk macronutrients: Expression of breast milk (fore milk) will be performed at 1 and 4 months postpartum at the researcher’s office in the morning, using a Philips Single Electric Breast Pump under researcher supervision. The sample will be stored at − 20 °C in the laboratory at the Pontificia Universidad Javeriana for analysis. Content of macronutrients (carbohydrate, protein and fat) and energy in breast milk will be determined using the MIRIS Human Milk Analyzer, which uses infrared transmission spectroscopy and requires a human milk sample of 5 ml. Results will be recorded in the database.Breast milk prolactin: Determination of breast milk prolactin concentration will be performed using an Abcam ab226901 Human Prolactin SimpleStep ELISA kit. The procedure requires 2 ml of breast milk.Serum prolactin: To determine the maternal serum prolactin concentration, a non-probabilistic convenience subsample of 60 (20%) women will be selected. The blood sample will be taken at the laboratory of the institution, within 2 h of waking in the morning and before any food is consumed. The procedure will require 5 ml of maternal blood, which will be analyzed by ELISA (Abcam ab226901).

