#### Data management

To guarantee the quality of the data, four checks will be performed: i) double checking of the information recorded in the questionnaires; ii) breastfeeding support verification (questionnaire administered by an independent investigator) in all mothers who completed the follow up; iii) random selection of questionnaires to check the consistency between data entered in the database and questionnaires; and iv) preliminary database check to identify extreme data and missing data using IBM SPSS Statistics software version 24. The questionnaires containing the original information will be stored safely at the Pontificia Universidad Javeriana for five years and the digital database will be stored as a computer file with access code. Clinical visits for breastfeeding counselling will be scheduled on different days for control and intervention groups to avoid contamination bias.

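### Mother-reported exclusive breastfeeding is asked by the unblinded counsellor-researcher, although a blinded investigator already questions completing mothers at 4 months

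*Protocol article*

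**What the plan says.** Under Primary outcomes and variables, breastfeeding and EBF are "ascertained by asking the mother about infant feeding practices during the last 24 h". Sample size is built on EBF alone.

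Four places settle who asks:
- Randomization and masking: "It will not be possible to blind the researcher performing the intervention and collecting data, although laboratory measurements will be blinded".
- Measures, infant 24-h recall: "The counsellor will ask about the initiation, frequency and mode of preparation of specific beverages and semisolid foods or supplements since the last visit".
- The closing sentence of Measures assigns all questionnaires and assessments to the researcher.
- Table 2 names the researcher as responsible for every intervention session.

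A second person also appears. In the counselling register item of Measures: "A questionnaire will also be administered by an independent investigator blinded to group allocation at the end of the study period". The listed content is problems identified, solutions and success. Data management describes the same check as a "questionnaire administered by an independent investigator) in all mothers who completed the follow up". Study design sets the primary end-point at 4 months, so this contact falls at the time that matters.

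**The concern.** EBF has no objective check in this trial. The other primary outcomes, infant growth and maternal weight, are measured, but neither confirms whether an infant was exclusively breastfed. The result depends on what the mother says and how the answer is heard.

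In the intervention arm the listener is the person with whom she agreed solutions towards EBF. That listener knows the arm and has an interest in the answer. Blinding the delivery of counselling is impossible, but blinding the feeding question is not, and the plan already has someone placed to do it.

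If over-reporting differs between arms, the excess is added directly to the estimated effect. Without a second, independent record, no later analysis can separate it from a true effect.

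**Working it through.** **Inputs from the protocol (Sample size).** Control EBF 22.8%; difference 23 points, so 45.8% in the intervention arm; power 95%; two-sided alpha 5%; losses 20%; 290 dyads, 145 per arm.

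**The plan's own figure.** The two-proportion formula is
n = [1.96·√(2·p̄·(1−p̄)) + 1.645·√(p₁(1−p₁) + p₂(1−p₂))]² / (p₂−p₁)², with p̄ = 0.343.
This is (1.316 + 1.071)² / 0.0529, or 108 per arm. The continuity correction raises it to 117. Then 117/0.8 = 147 per arm (294 in all), or 117 × 1.2 = 141 per arm (282 in all). Both lie within 3% of 290, so the stated size is sound. Analysed number after losses: 145 × 0.8 = 116 per arm.

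**Assumption, not in the documents.** A fraction f of non-EBF mothers in the intervention arm, and g in control, report EBF. There is no true effect: 22.8% in both arms.

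Reported rates are 0.228 + 0.772·f and 0.228 + 0.772·g, so the false difference is 0.772·(f − g). The chance of a significant result favouring the intervention is
Φ[(difference − 1.96·SE₀)/SE₁],
where SE₀ = √(2·p̄·(1−p̄)/116), p̄ is now the mean of the two reported rates, and SE₁ uses each arm's own variance.

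Example, f = 10%, g = 0: reported 30.5% against 22.8%; difference 0.0772; SE₀ = 0.0581; SE₁ = 0.0578; (0.0772 − 0.1138)/0.0578 = −0.63; Φ = 0.26.

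| f (intervention) | g (control) | Reported EBF, intervention vs control | False difference | Chance of significant benefit |
|---|---|---|---|---|
| 10% | 0% | 30.5% vs 22.8% | 7.7 points | 26% |
| 15% | 0% | 34.4% vs 22.8% | 11.6 points | 50% |
| 20% | 0% | 38.2% vs 22.8% | 15.4 points | 73% |
| 20% | 5% | 38.2% vs 26.7% | 11.6 points | 47% |
| 20% | 10% | 38.2% vs 30.5% | 7.7 points | 23% |

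The nominal chance is 2.5%. Equal over-reporting (f = g) gives no false difference. With g = 0, the whole planned 23-point effect would need f = 0.23/0.772 = 29.8%.

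**The case against.** The strongest reply is that the lack of blinding is openly stated, and that the same researcher sees both arms. Control mothers meet this researcher at the data-collection visits and are also advised by the institution to breastfeed exclusively for six months. Mothers are told there are two kinds of support but not the details. A wish to please is therefore plausible in both arms, and only the excess in the counselled arm biases the comparison. This stands, and it is why the control-arm range is shown.

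It is also true that a blinded interviewer cannot stop a counselled mother from knowing she was counselled, and that the 1- and 3-month recalls would remain with the researcher. Both limit the benefit of the change.

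Four stronger readings are tempting, and the text does not support them:
- That the protocol wrongly presents a single data collector as the answer to reporting bias. The sentence "Data collection will be performed by the same researcher in both groups to control information bias among observers" closes the infant anthropometry item and concerns differences between observers. One measurer does control those.
- That visit days unmask the blinded contact. Visits "scheduled on different days for control and intervention groups to avoid contamination bias" are the counselling visits. Four months is not a counselling session, and nothing ties that contact to arm.
- That session after session is spent extracting a promise of EBF. Commitment is one sub-item of the pregnancy session in Table 2.
- That the blinded questionnaire covers counselling and nothing else. The text says what it will include. The fair statement is that feeding is not listed.

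**Conclusion.** The point holds in a limited form. The self-reported outcome behind the sample size is collected by the unblinded person who delivers the intervention, while a blinded contact at the primary end-point is not shown to be used for it.

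Under the assumed rates, the chance of a false positive lies between about 23% and 73%, depending on how far over-reporting in the counselled arm exceeds that in control. The calculation shows that reporting bias could produce a significant result. It does not show that it will, because the documents give no misreporting rates. A reader might infer that the bias acts in one arm only; the contact schedule and the standard advice to control mothers do not support that.

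The point covers breastfeeding and EBF, not the measured primary outcomes.

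There is also an internal conflict. The closing sentence of Measures gives every questionnaire to the researcher, while the counselling register item and Data management give one to an independent investigator. The remedy depends on that investigator, so the passages must be reconciled.

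**What to change.** 1. At the existing 4-month contact, have the blinded investigator ask the infant-feeding items (last 24 h and since the last visit) in both arms, before any counselling question, because counselling content may reveal the arm.
2. Declare that record the primary 4-month EBF measurement in both arms.
3. Keep the researcher's recall as a secondary source and report agreement between the two by arm. Disagreement that differs by arm would be evidence of differential reporting.
4. Reconcile the closing sentence of Measures with the counselling register item and Data management, so that the independent investigator's role is unambiguous.

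**Cost.** A few added questions at a contact already planned for all completing mothers; no new staff or visit, and no change to the 290 dyads. It needs an amendment. Because the trial was registered retrospectively, some mothers may already have been assessed, so the amendment needs a rule for which record counts for them. The 1- and 3-month recalls stay unblinded, and the bias at 4 months is reduced rather than removed, because mothers may know their arm.

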#### Data collection

Data will be collected from all participants at five study time-points (last month of pregnancy, 24 h postpartum, and 1, 3 and 4 months postpartum) as described in Table 1. Questionnaires and assessments (detailed description below) will be completed at study visits as described in Figs. 1 and 2. The main information will be: i) sociodemographic and maternal and paternal health status questionnaire (last month of pregnancy); ii) maternal food consumption pattern measured using a maternal 24 h dietary recall [58, 59] and a semiquantitative food frequency questionnaire adapted for foods available in Colombia in a previous pilot study as described below; iii) maternal intention to breastfeed using the Infant Feeding Intention Scale adapted from the Nommsen-Rivers scale [60] (last month of pregnancy); iv) maternal risk of postpartum depression using the EPDS [54] (late gestation and 1 month postpartum); v) maternal physical activity using the IPAQ short version [61]; and vi) mother and infant anthropometric measurements. Breast milk macronutrient content will be determined at 1 and 4 months postpartum using infrared transmission spectroscopy (MIRIS Human Milk Analyzer) and serum and milk prolactin concentration will be determined by in vitro ELISA commercial kit.

**Table 1 Tab1:** Study variables and data collection questionnaires to be used in the study

Time-point	Questionnaire or assessment	Description
Last month of gestation	General information	Name, address, phone number, maternal ID, maternal date of birth, health social scheme.
	Maternal socioeconomic and demographic information	Marital status, socioeconomic level, type of housing, maternal occupation, monthly income, educational level, maternal leave, income assigned to food purchase, access to tap water, person in charge to infant, breastfeeding family support.
	Pregnancy information	Maternal smoking, obstetric background, gestational age, probable date of birth, supplement and vitamins intakes, laboratory reports, medical history.
	Paternal information	Educational level, monthly income, weight and height (self-reported), medical history.
	Intention to breastfeed	Five questions about intention to breastfeed or give formula until 6 months postpartum.
	Maternal anthropometry	Pregestational weight (self-reported), weight, height and MUAC measurements.
	Breast examination	Nipple and breast self-perception.
	Counselling assessment	Detected problems and concerted solutions.
	IPAQ SV	Physical activity registry: type of activity, time (minutes per day), number of days per week.
	EPDS	Ten questions to evaluate maternal emotional status.
	Maternal 24-h dietary recall	Five steps 24HR: fast list, frequently forgotten foods, meals and time, food consumption in the last 24 h within detailed registry and standardized recipes.
	Semi-quantitative food frequency intake	Diary, weekly or monthly intake of 107 foods included in 8 food groups.
24 h postpartum	Maternal anthropometry Information about delivery and newborn	Weight and MUAC. Gender, date of birth, type of delivery, complications, gestational birth age, APGAR at 5 min, time of birth.
	Newborn anthropometry	Birth weight, length, head circumference, MUAC.
	Breastfeeding information	Time of skin to skin contact, duration of skin to skin contact, breastfeeding during the first hour after delivery, breastfeeding difficulties.
	Infant 24-h recall	Time, place, infant feeding in the last 24 h (including breastfeeding, infant formula or other type of foods given to the baby).
	Breast milk intake	Number of breastfeeds per day and night, time per each breastfeed, appetite (mother’s perception).
	Breast latching	Observation of latching, swallowing, type of nipple, maternal comfort perception and breastfeeding position.
	Counselling registry at 24 h, 3th day, 7th day and 14th day	Detected problems and agreed solutions, success of breastfeeding counselling regarding the last meeting’s concerted solutions.
1 month postpartum	Maternal anthropometry	Weight and MUAC.
	Infant anthropometry	Weight, length, head circumference, MUAC.
	Counselling registry	Detected problems and concerted solutions, success of breastfeeding counselling regarding the last meeting’s concerted solutions.
	IPAQ SV	Physical activity registry: type of activity, time (minutes per day), number of days per week.
	EPDS	Ten questions to evaluate maternal emotional status.
	Maternal 24-h recall	Five steps 24HR: fast list, frequently forgotten foods, meals and time, food consumption in the last 24 h within detailed registry and standardized recipes.
	Semi-quantitative food frequency intake	Diary, weekly or monthly intake of 107 foods, included in 8 food groups.
	Infant 24-h recall	Time, place, infant feeding in the last 24 h (including breastfeeding, infant formula or other type of foods given to the baby).
	Breast milk intake	Number of breastfeeds per day and night, time per each breastfeeds, appetite (mother’s perception).
	Breast milk macronutrient content	Protein, lactose and fat content in human milk
	Prolactin in maternal serum	Concentration of prolactin hormone in maternal serum, 2 h after maternal wake up
3 months postpartum	Maternal anthropometry	Weight and MUAC.
	Infant anthropometry	Weight, length, head circumference, MUAC.
	Breast examination	Nipple and breast observation.
	Counselling registry	Detected problems and concerted solutions, applicability of last meeting’s concerted solution
	Infant 24-h recall	Time, place, type of food.
	Breast milk intake	Number of breastfeeds per day and night, time per each breastfeed, appetite (mother’s perception).
	Macronutrients content in breast milk	Protein, lactose and fat content in human milk.
	Prolactin in maternal serum	Concentration of prolactin hormone in maternal serum, 2 h after maternal wake up.
4 months postpartum	Maternal anthropometry	Weight and MUAC.
	Infant anthropometry	Weight, length, head circumference, MUAC.
	Breast examination	Nipple and breast observation.
	Assessment of breastfeeding counselling	Successful of new approach in EBF counselling with 5 questions to assess concerted solutions.
	IPAQ SV	Physical activity registry: type of activity, time (minutes per day), number of days per week.
	Maternal 24-h recall	Five steps 24HR: fast list, frequently forgotten foods, meals and time, food consumption in the last 24 h within detailed registry and standardized recipes.
	Semi-quantitative food frequency intake	Diary, weekly or monthly intake of 107 foods, included in 8 food groups.
	Infant 24-h recall	Time, place, infant feeding in the last 24 h (including breastfeeding, infant formula or other type of foods given to the baby).
	Breast milk intake	Number of breastfeeds per day and night, time per each breastfeed, appetite (mother’s perception).

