#### Secondary hypotheses

Compared to standard management, the implementation of a new EBF counselling intervention designed to support overweight woman will result in:
i)An increase in the volume of breast milk in ml as a result of an increase in serum prolactin levels in ng/ml, at 1 and 4 months.ii)Higher milk prolactin concentration and adequate macronutrient content of protein, lactose, fat and energy, at 1 and 4 months, which will in turn be associated with more optimal infant growth (based on WHO growth standards).

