### Secondary outcomes and variables

i)Maternal serum levels of prolactin and breast milk prolactin concentration and macronutrient content, measured at 1 and 4 months after delivery;ii)Estimated breast milk intake at 1 and 4 months according to WHO recommendations [53].

The study design is shown in Fig. 1 and a timeline of measurements in Fig. 2.

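### Table 1 places the second milk and serum sample at 3 months, while the outcome definitions and methods text place it at 4 months

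*Protocol article*

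**What the plan says.** Outcome definitions in the protocol article:

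- Secondary outcomes and variables: "Maternal serum levels of prolactin and breast milk prolactin concentration and macronutrient content, measured at 1 and 4 months after delivery".
- Secondary hypotheses, first item, on milk volume: "as a result of an increase in serum prolactin levels in ng/ml, at 1 and 4 months".
- Secondary hypotheses, second item: "Higher milk prolactin concentration and adequate macronutrient content of protein, lactose, fat and energy, at 1 and 4 months".

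Methods text:

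- Data collection: "Breast milk macronutrient content will be determined at 1 and 4 months postpartum". The same sentence gives the prolactin assay but no month for it.
- Measures, breast milk macronutrients: "Expression of breast milk (fore milk) will be performed at 1 and 4 months postpartum". The milk prolactin and serum prolactin entries in this section give no month.

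Table 1 (in Data collection):

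- The 1-month block has a milk macronutrient row and a serum prolactin row.
- The 3-month block has both again, the first as "Macronutrients content in breast milk".
- The 4-month block has nine rows, ending with breast milk intake, and none is a laboratory sample.
- Milk prolactin has no row of its own at any visit.

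The serum draw time is also given in two ways. Table 1 has "Concentration of prolactin hormone in maternal serum, 2 h after maternal wake up". The serum prolactin entry in Measures has "within 2 h of waking in the morning and before any food is consumed".

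**The concern.** The Data collection and Measures sections both point to Table 1 for what is collected at each visit. Someone who works from the table would take the second milk and blood sample at 3 months and none at 4.

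Four months is the primary end-point in Study design, and the second secondary hypothesis ties milk composition at 1 and 4 months to infant growth. A sample not taken at 4 months cannot be obtained later, and no analysis plan can repair the gap.

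Two features of the schedule make 3 months a poor stand-in:

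- It is the visit at which the last listed counselling session takes place, so a sample taken then cannot reflect what follows from that session.
- Table 1 schedules the maternal diet recall, food frequency and physical activity questionnaires at 1 and 4 months but not at 3. Measures names maternal diet as a potential confounder, so a 3-month milk sample would have no diet data from the same visit.

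**Working it through.** The plan states no figure to reproduce. The check compares the months required by the text with the months listed in Table 1.

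| Secondary outcome | Text | Source of the months | Table 1 | In text, not in table | In table, not in text |
|---|---|---|---|---|---|
| Milk macronutrients | 1, 4 | Secondary hypotheses; Secondary outcomes; Data collection; Measures (milk expression) | 1, 3 | 4 | 3 |
| Serum prolactin | 1, 4 | Secondary hypotheses; Secondary outcomes | 1, 3 | 4 | 3 |
| Milk prolactin | 1, 4 | Secondary hypotheses; Secondary outcomes | no row | 1, 4 | none |
| Estimated milk intake (not a laboratory measure) | 1, 4 | Secondary outcomes | 1, 3, 4 (also at 24 h postpartum) | none | 3 |

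**Number of samples.** Sample size sets a laboratory subsample of 60 women, 30 per group, covering prolactin and macronutrients. Two occasions give 60 × 2 = 120 sampling occasions. The second set is 60 of these, and 60 / 120 = 50%. Under Table 1 those 60 fall at 3 months, which is 4 − 3 = 1 month before the visit named in the outcome definition. The count assumes that every woman attends both visits.

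**Is this a fault of reproduction?** It is unlikely. The 3-month laboratory rows are complete and sit inside their block. Even if rows had dropped off the end of the 4-month block, the 3-month rows would still conflict with the text.

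**Draw time.** Table 1 reads as a point 2 h after waking. Measures reads as any time from 0 to 2 h after waking, before food. The two meet only at the 2 h limit, so they are different instructions.

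**The case against.** The strongest reply is that this is a placement slip of limited reach. Every piece of running text that gives months for these measures says 1 and 4, and only the table differs. Data collection also refers to Figs. 1 and 2, and the Fig. 2 caption mentions the milk and serum samples. Neither figure is available here, and either may carry the 4-month visit. One researcher administers all assessments, which lowers the chance that someone works from the table alone. All of this stands. It reduces the likelihood of the error but leaves the contradiction in place.

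A reader might also infer more than the document supports:

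- *That the second time-point disappears.* It does not. A second sample would be taken, at 3 months, and what is lost is the 4-month value.
- *That milk prolactin would not be sampled.* It is assayed on 2 ml of breast milk, and Table 1 already schedules milk. The missing row is a labelling gap.
- *That the secondary hypotheses become untestable.* Feeding and growth are also measured at 3 months, so a 3-month sample could be set against them. It would miss the planned time and the primary end-point.
- *That all four text sections fix the serum months.* Only the secondary hypotheses and secondary outcomes do.
- *That the unsettled draw time biases the comparison through suckling.* Time since waking is not time since suckling, so settling one draw time would not control a suckling response. A difference between arms that arises from feeding frequency could itself be an effect of the intervention. The document gives no ground for requiring an extra time-since-feed field.

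**Conclusion.** The contradiction is real and is in the current text. For milk macronutrients and serum prolactin, Table 1 gives 1 and 3 months where the outcome definition gives 1 and 4. Milk prolactin is missing from the table as a named item.

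If the table is followed, the 4-month value of the laboratory secondary outcomes is lost for good: half of the planned sampling occasions in a subsample of 60, taken one month early. This rests on two assumptions: that the table rather than the text guides sampling, and that the figures not shown do not override it.

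The reach is limited to secondary outcomes. Prolactin is confined to the subsample. Sample size places macronutrients there too, although the macronutrient entry in Measures does not repeat that limit. The primary outcomes, estimated milk intake and the sample size calculation are unaffected. This is a worthwhile correction of moderate weight and does not threaten the trial's main conclusions. The draw-time mismatch is minor.

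**What to change.** 1. In Table 1, move the milk macronutrient and serum prolactin rows from the 3-month block to the 4-month block, to match the secondary outcome definition.
2. Name milk prolactin alongside the milk sample at 1 and 4 months.
3. Add the months to the serum and milk prolactin entries in Measures, and check that Figs. 1 and 2 agree.
4. Reconcile the serum draw time so that Table 1 and Measures give one instruction.

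The cost is an edit to one table and a few words of text. The number of samples, visits and women stays the same. If any sampling has already followed the table, the report should state the actual visit of each sample.
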